### (4) Dark purple lips

0 point: none;

1 point: light dark lips;

2 points: dark lips with stasis spots;

3 points: dark purple lips with ecchymosis.

### (5) Dark purple tongue

0 point: normal or other conditions;

1 point: light dark purple tongue.

2 points: dark purple tongue with stasis spots.

### (6) Fine-choppy pulse

0 point: normal or other conditions;

1 point: fine-choppy pulse.

### 4.4.2 Severity classification

Mild: TCM syndrome score  $\leq 6$  points;

Moderate: TCM syndrome score 6 -10 points;

Severe: TCM syndrome score  $\geq 11$  points.

## 4.5 Eligibility criteria

#### **4.5.1 Inclusion criteria**

- Patients who fulfill the diagnostic criteria of stable angina pectoris;
- Patients who fulfill the diagnostic criteria of CCS grading class I , II or III;
- Patients who fulfill the diagnostic criteria of blood stasis syndrome;
- Patients who have angina attacks  $\geq 2$  episodes per week;
- Ischemic changes on ECG: ST segment depression  $\geq 0.05\text{mv}$  and/or deep T wave inversions  $> 0.2\text{mv}$ , flat T wave less than  $1/10R$ , or positive exercise stress test.
- Aged 40-70 years.
- Those who are willing to provide a signed informed consent form.

#### **4.5.2 Exclusion criteria**

- Those who do not fulfill the inclusion criteria;
- Those who have documented acute myocardial infarction or other heart diseases, severe neurosis, menopausal syndrome, hyperthyroidism, cervical spondylosis, gallbladder-heart disease, or gastroesophageal reflux;
- Those who are complicated with poorly-controlled hypertension (systolic BP  $\geq 160\text{mmHg}$ , and/or diastolic BP  $\geq 100\text{mmHg}$ ), severe cardiac or pulmonary insufficiency, severe arrhythmia (e.g. rapid atrial fibrillation, atrial flutter, paroxysmal ventricular tachycardia), serious primary diseases of liver, kidney or hematopoietic system, or psychosis;
- Those who have obtained a complete revascularization after coronary artery bypass grafting or coronary intervention;
- Pregnant or lactating women;
- Those who are prone to allergies or with known allergy to many drugs;
- Those who participated in other clinical trials within 1 month prior to randomization.

#### **4.5.3 Withdrawal/dropout criteria**

- Those who did not fulfill the eligibility criteria but were included by mistake;
- Those who fulfilled the eligibility criteria but did not take any study drug after randomization;
- Those with poor compliance that might interfere with the efficacy and safety evaluation;

- Those who experienced serious AEs, complications or special physiological changes, making it inappropriate to continue with the trial;
- Individual cases that were unblinded prematurely;
- Those who discontinued the trial voluntarily;
- Those who used any disallowed concomitant medication, especially those that had an obvious effect on the study drug and might interfere with the efficacy and safety evaluation;
- Those who discontinued or lost to follow-up for any other reasons or died during the trial;
- Those with incomplete data that might interfere with the efficacy and safety evaluation.

For all withdrawal/dropout cases, the potential reasons must be recorded. Patients who experienced any AE during the trial must be included in the statistical analysis of adverse drug reactions. Those who have taken the study drug for at least 1 week should be included in the statistical analysis of drug efficacy.

#### **4.5.4 Criteria for study termination**

Circumstances that may warrant termination include, but are not limited to:

- Identification of unexpected, significant, or unacceptable risk to subjects;
- Poor efficacy or no efficacy of the study drug;
- Major mistakes in the trial protocol;
- Insufficient adherence to protocol requirements;
- Upon sponsor's request (e.g. economic or administrative reasons).

#### **4.5.5 Criteria for subject discontinuation**

- Any allergic reaction or AE occurs such that continued participation in the study would not be in the best interest of the subject at the discretion of the treating physician;
- Worsening of clinical conditions occurs such that continued participation in the study would not be in the best interest of the subject at the discretion of the treating physician; considered as ineffective cases;
- Subjects are free to withdraw from participation in the study at any time upon

request.

In any case, every effort must be made to determine why patients discontinued the study treatment prematurely, which may include but are not limited to poor confidence in efficacy, occurrence of AEs, SAEs, or other serious complications, worsening of symptoms such that emergent intervention is required. As for those who withdrew from participation in the study or lost to follow-up, it is essential to investigate the potential reasons via telephone or mail. Investigators should record in detail when and how the last dose was administered, the efficacy and safety parameters at and after discontinuation, the relationship between discontinuation or withdrawal and the study drug, and the potential impact of discontinuation cases on the final conclusion of the study. Moreover, case report form (CRF) of withdrawal/dropout cases should also be completed and their original data should also be documented and stored in a secure manner.

## **5 TEARTMENT REGIMEN**

### **5.1 Origins of study drugs**

Trial drug: XXK capsule, manufactured by Chengdu Di'ao Pharmaceutical Group Co. Ltd., Lot No.: 200807081; Approval No.: Z10910051

Control drug: CDS tablet, manufactured by Chengdu Di'ao Pharmaceutical Group Co. Ltd., Lot No.: 081002

Placebo of CDS tablet: manufactured by Chengdu Di'ao Pharmaceutical Group Co. Ltd., Lot No.: 081001

Placebo of XXK capsule: manufactured by Chengdu Di'ao Pharmaceutical Group Co. Ltd., Lot No.: 200807081

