**Study site No.:**

**Drug No.:**

**For use of post-marketing study of  
Xinxuekang capsule**

**Functions and indications:** promoting blood circulation and removing blood stasis, removing obstruction from the meridians and collaterals, and relieving pain. Coronary heart disease with angina pectoris (blood stasis syndrome) is indicated.

**Dosage and administration:** for oral use, 1 or 2 capsules a time, 3 times a day.

**Duration of treatment:** 20 weeks.

**Strength:** 10 capsules/blister × 2blisters/box

**Storage:** sealed and stored at the room temperature

**Lot No.:** 200807081

**Storage life:** 2 years

**Supplied by:** Chengdu Di'ao Pharmaceutical Group Co. Ltd.

An emergency envelop is inserted into each package, indicating the actual drug name and treatment allocation; and information on how to store this envelop and when to open it is provided on the envelop surface. The distribution process of the study drugs should be well-documented.

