### **5.3 Accountability procedures for study drugs**

Upon receipt of the study drugs from the sponsor, investigator or designated individual at each study site should sign a “Receipt form of study drugs” to ensure that the information on the packing slip matches exactly with what has been sent to the site, including the amount, lot numbers and quantity. When an eligible subject is included, investigator or designated individual will dispense the proper drugs in strict accordance with the randomization list. Each time a study drug is dispensed, there should be a “Drug dispensing form” as to the amount dispensed, to whom it is dispensed, and the date and signature of the person dispensing the drug.

Subjects should be advised to return all unused drugs at each study visit. Study personnel should record the amount (number of capsules) and date of return. Study drug will be properly accounted for and tracked with adequate documentation so as to assess subject's compliance.

The study drugs should be stored in a dry and ventilated place at room temperature.

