### **5.4 Study treatment**

#### **5.4.1 Drug administration**

(1) trial group: XXK capsule + placebo of CDS tablet, oral, 2 capsules + 2 tablets a time, 3 times a day;

(2) control group: CDS tablet + placebo of XXK capsule, oral, 2 tablets + 2 capsules a time, 3 times a day.

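### Active and placebo tablets carry different lot numbers that are printed in the site-held protocol and checked at site, with no masking described: an avoidable risk to the blind

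*Protocol*

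**What the plan says.** Protocol section 5.1 lists four products with their lots. The two tablets differ: "Control drug: CDS tablet, manufactured by Chengdu Di'ao Pharmaceutical Group Co. Ltd., Lot No.: 081002" for the active product and "Placebo of CDS tablet: manufactured by Chengdu Di'ao Pharmaceutical Group Co. Ltd., Lot No.: 081001" for its dummy. The two capsules do not: "Trial drug: XXK capsule, manufactured by Chengdu Di'ao Pharmaceutical Group Co. Ltd., Lot No.: 200807081" and "Placebo of XXK capsule: manufactured by Chengdu Di'ao Pharmaceutical Group Co. Ltd., Lot No.: 200807081".

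Section 5.4.1 assigns the products to arms. In the XXK arm it is "trial group: XXK capsule + placebo of CDS tablet, oral, 2 capsules + 2 tablets a time, 3 times a day"; the control arm takes the active tablet with the dummy capsule.

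Section 5.3 sets the receipt procedure. The "investigator or designated individual at each study site should sign a" receipt form, confirming that the packing slip "matches exactly with what has been sent to the site, including the amount, lot numbers and quantity". The same role then dispenses the drug.

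Other relevant text:

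- Section 3.5 describes a double-blind, double-dummy comparison.
- Section 5.2 states that the sponsor packages and supplies all drugs blinded. The one label it reproduces has a line for a drug number and a lot line, "Lot No.: 200807081", which is the capsule lot.
- Section 6.2 has the physician in charge at each centre administer the angina score behind the angina-free endpoint, and also the syndrome score.
- Section 14.1 places the protocol and its amendments in the investigator's file at every site.

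**The concern.** In a double-dummy trial the two arms' supplies should look the same to everyone at the site, in their paperwork as well as in appearance. Here the protocol itself holds a table that translates a tablet lot into a treatment, and its own receipt procedure directs site staff to look at lot numbers.

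If a tablet lot could be read on a numbered bottle or kit, anyone with the protocol could work out that patient's arm. The emergency envelopes are controlled by sections 3.5 and 8.6: opening one has to be documented and signed, and the patient is withdrawn. Reading a lot number would leave no such record.

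The blind matters here because being angina-free, one of the two primary endpoints, rests on a physician-administered symptom score that can move with expectation. The protocol does not require the person who handles drug supply to be different from the person who enrols or scores patients.

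**Working it through.** No sample size, power or error-rate figure enters this point, so there is nothing to recompute. The check sets the sections side by side.

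**Step 1: does the lot identify the arm?** Combine the lots in section 5.1 with the arm contents in section 5.4.1.

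| Product | Lot | XXK arm | Control arm |
|---|---|---|---|
| XXK capsule, active | 200807081 | yes | no |
| XXK capsule, dummy | 200807081 | no | yes |
| CDS tablet, active | 081002 | no | yes |
| CDS tablet, dummy | 081001 | yes | no |

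The capsule lot occurs in both arms and carries no information. Each tablet lot occurs in one arm only, so a known tablet lot fixes the arm.

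**Step 2: do sites hold the key?** Yes. The key is in the body of section 5.1, and section 14.1 puts the protocol in each site's file.

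**Step 3: are sites told to look at lots?** Yes, on receipt. Section 5.3 names lot numbers among the items to be matched, and the investigator may do this in person.

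**Step 4: is the tablet lot masked?** No section says so. Section 5.2 asserts blinded packaging in general terms but does not say how two different tablet lots are kept from view, and it does not reconcile that with the lot check in section 5.3.

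**Step 5: is a lot tied to a patient?** Not in the text. The receipt check concerns a consignment. The dispensing form in section 5.3 records amount, recipient, date and signature; the return record holds amount and date. Neither lists a lot. The final allocation in section 3.3 is 92 patients per arm at each site, so a site's supply as a whole must contain both tablet products. Seeing both lots on a packing slip identifies nobody unless the slip, bottle or kit links a lot to a drug number.

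Steps 1 to 4 are settled by the text. Step 5 is the missing link, and it depends on a label and a packing slip that the protocol does not show.

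**The case against.** The strongest reply is that no unblinding is shown. Nowhere does the protocol say that 081001 or 081002 is printed on a bottle, a kit or a patient record. The only label reproduced carries the capsule lot, which is the same in both arms. Section 5.2 says packaging is blinded. The receipt check is of a shipment and may be delegated to someone who neither enrols nor scores. Matching lots on receipt is also an ordinary accountability step.

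Most of this stands, and it rules out three stronger readings that a reader might infer:

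- *That the tablet lot does reveal the arm to those who enrol and score.* This needs a readable lot on a numbered package, which is plausible given the lot line on the label shown, but is not documented. The text also does not make the drug handler and the scoring physician the same person; it only fails to keep them apart.
- *That staff can foresee the next allocation.* This needs a link from lot to drug number before dispensing, and the documents contain none.
- *That a given part of the treatment difference could be due to this.* The documents offer no basis for how many scores would shift, so any such figure would be invented.

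What the reply does not remove is the key itself. A general statement of blinded packaging does not explain how the differing lots are hidden, and the receipt check pulls the other way, since a match against the goods normally requires that the lots can be read on them or on their outer packaging. Delegation is allowed but not required.

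**Conclusion.** The point holds as a risk. The protocol prints a complete key from tablet lot to arm, places it at every site and instructs site staff to check lots, while describing no masking of the tablet lots. That creates an avoidable route to unblinding wherever a tablet lot is readable on a numbered bottle or kit.

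It does not hold as a demonstrated failure of the blind, and no size of bias can be derived. The conclusion assumes that the tablets supplied come from the lots listed in section 5.1 and that the actual tablet labels and packing slips, which are not shown, are not already coded. If they are coded, the route is closed in practice and only the protocol wording needs correcting. The shared capsule lot is relevant only as a contrast: it shows a labelling arrangement that gives nothing away, which the tablets lack.

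This is a cheap improvement that protects a physician-scored primary endpoint. It is not a defect that by itself invalidates the design.

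**What to change.** - In section 5.1, remove the tablet lot-to-product key from the text held by sites, and keep the true lots in a supply file restricted to the sponsor's unblinded staff.
- In section 5.2, state that active and placebo tablet bottles, and the packing slips that accompany them, carry one common study code.
- In section 5.3, replace the lot match on receipt with reconciliation by drug number and quantity.

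The cost is a wording change in these sections and a common label for the tablet bottles. The downside is that a site can no longer trace a tablet batch itself: a quality query or recall has to run through the sponsor's supply file.

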### **5.2 Packaging of study drugs**

All drugs used in the study are packaged and supplied by the sponsor in a randomized and blinded manner.

#### **(1) Strength**

XXK capsule: 100mg steroidal saponins/capsule, 10 capsules/blister × 2 blisters/box

CDS tablet: 0.25g×60 piles/bottle

#### **(2) Labeling**

**Approval number:** Z10910051

**Study site No.:**

**Drug No.:**

**For use of post-marketing study of  
Xinxuekang capsule**

**Functions and indications:** promoting blood circulation and removing blood stasis, removing obstruction from the meridians and collaterals, and relieving pain. Coronary heart disease with angina pectoris (blood stasis syndrome) is indicated.

**Dosage and administration:** for oral use, 1 or 2 capsules a time, 3 times a day.

**Duration of treatment:** 20 weeks.

**Strength:** 10 capsules/blister × 2blisters/box

**Storage:** sealed and stored at the room temperature

**Lot No.:** 200807081

**Storage life:** 2 years

**Supplied by:** Chengdu Di'ao Pharmaceutical Group Co. Ltd.

An emergency envelop is inserted into each package, indicating the actual drug name and treatment allocation; and information on how to store this envelop and when to open it is provided on the envelop surface. The distribution process of the study drugs should be well-documented.

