### REGIMEN:

Trial group: XXK capsule + placebo of CDS tablet, oral, 2 capsules + 2 tablets a time, 3 times a day;

Control group: CDS tablet + placebo of XXK capsule, oral, 2 tablets + 2 capsules a time, 3 times a day.

---

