### 6.2 Efficacy parameters

The primary efficacy endpoint of this study is:

- Proportions of patients who were angina-free.

Angina-free was defined as the responses of patients' anginal symptoms were "none" on the Quantification Score of Angina Pectoris (see page 19 for details) including three dimensions (attack frequency, severity and duration of angina) over the 20-weeks treatment phase. The Quantification Score of Angina Pectoris comprising questions investigating the patients' anginal symptoms was administered by the physician in charge of the study at 2, 4, 6, 8 and 20 weeks in each center.

- Proportion of effective electrocardiogram (ECG) improvement.

The effective ECG improvement was defined as a standard 12-lead ECG returns to normal(or within the normal range) according to the International Society and Federation of Cardiology/World Health Organization after 20-weeks long term treatment. The ECG was performed at 0,8, and 20 weeks during treatment.

Secondary efficacy endpoints are:

- Change from baseline in weekly average frequency of self-reported angina episode over the 20-weeks treatment phase.
- Weekly average nitroglycerin consumption rate at week 8 and week 20.

Throughout the study, patients recorded the occurrence of anginal attacks and the number of nitroglycerin use on diary cards and the study staff at each clinical site reviewed the angina and nitroglycerin use cards with the patient at each study visit(2, 4, 6, 8 and 20 weeks) to ensure accuracy.

- Change from baseline in 5 dimensions of the Seattle Angina Questionnaire (SAQ) and the proportions of patients who were clinical significance at week 8 and week 20.

The SAQ is a disease-specific functional status measure that was developed to quantify the physical and emotional effects of CAD[6].Each SAQ dimension (anginal frequency, physical limitation, anginal stability, disease perception, and treatment satisfaction) was scored on a scale of 0 to 100 and the clinical significance was defined as a difference of 8 points or more on the physical-limitation scale, 25 or more on the angina-stability scale, 20 or more on the angina-frequency scale, 12 or more on the treatment-satisfaction scale, and 16 or more on the quality-of-life scale[7].Patients will complete the SAQ at 0,8, and 20 weeks.

- Change from baseline in the blood stasis syndrome and the proportion of patients who had significant syndrome improvement.

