### **12.2 Investigator training**

All investigators at each study site should attend a training session before participation to have a deep understanding of all the requirements in the conduct of the clinical trial.

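### The study-pack label permits 1 or 2 capsules per intake while the regimen fixes 2, so a patient who obeys the label can take half the XXK dose and be classed as poorly compliant

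*Protocol*

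**What the plan says.** Section 5.2, (2) Labeling, gives the text of the capsule label. It has fields for the site and drug numbers, the statement "For use of post-marketing study of" the XXK capsule, and a 20-week treatment duration. Its dosing line reads "for oral use, 1 or 2 capsules a time, 3 times a day".

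The regimen is stated twice elsewhere, without a range. For the trial group, section 5.4.1 specifies "XXK capsule + placebo of CDS tablet, oral, 2 capsules + 2 tablets a time, 3 times a day". For the control group, the synopsis specifies "CDS tablet + placebo of XXK capsule, oral, 2 tablets + 2 capsules a time, 3 times a day". The two sections agree for both arms. No section provides for a one-capsule dose, titration or dose reduction.

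Section 5.2, (1) Strength, gives the content: "XXK capsule: 100mg steroidal saponins/capsule". Section 12.3 defines compliance as the amount taken divided by the amount due, and treats values below 80% or above 120% as poor. Section 11.1.1 makes compliance a condition for the per protocol set (PPS) and has the primary outcomes analysed in both the full analysis set (FAS) and the PPS. Section 4.5.3 lists poor compliance that might interfere with evaluation among the withdrawal/dropout criteria.

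**The concern.** The label is the written instruction on the pack the patient takes home, and it is looser than the regimen. Two capsules per intake satisfy both texts. One capsule satisfies the label and breaks the regimen.

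Three things are at stake:

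- **Dose.** The capsule is active only in the XXK arm, so single-capsule dosing halves the test drug there. In the control arm it omits only placebo.
- **Analysis set.** A patient who follows the printed instruction can be counted as poorly compliant and lost from the PPS, in either arm.
- **The compliance denominator.** Section 12.3 divides by what the patient should have taken. Measured against section 5.4.1, one capsule per intake is half of what is due. Measured against the label, it could pass as full compliance. The protocol should not leave both readings open.

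**Working it through.** The protocol states no figure on this point to reproduce, so the check is direct arithmetic from its own definitions.

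**Inputs**

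- Duration 20 weeks (5.4.2); three intakes a day, each of 2 capsules and 2 tablets (5.4.1 and synopsis).
- 100 mg per XXK capsule (5.2).
- Compliance = taken / due × 100%, with a lower limit of 80% (12.3).
- Visits after baseline at weeks 2, 4, 6, 8 and 20 (6.2 and the flowchart in section 15).
- Assumptions: section 5.4.1 defines the amount due; all tablets are taken; placebo-capsule packs carry the same dosing line, as blinding would require.

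**Amount due**

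- Intakes: 20 × 7 × 3 = 420.
- Capsules: 420 × 2 = 840. Tablets: 420 × 2 = 840. Together 1,680 units.
- XXK per day: 6 × 100 = 600 mg. At one capsule per intake: 3 × 100 = 300 mg.

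**Compliance when n of the 420 intakes use one capsule**

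Section 12.3 does not say whether capsules and tablets are counted separately or together, so both counts are shown:

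- Capsules alone: (840 − n) / 840.
- Pooled: (1,680 − n) / 1,680.

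| Pattern | n | Capsules alone | Pooled |
|---|---|---|---|
| One capsule at every intake | 420 | 420/840 = 50.0% | 1,260/1,680 = 75.0% |
| Weeks 0–2 only, then corrected | 14 × 3 = 42 | 798/840 = 95.0% | 1,638/1,680 = 97.5% |
| Weeks 8–20 only | 84 × 3 = 252 | 588/840 = 70.0% | 1,428/1,680 = 85.0% |

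**Where the 80% limit is crossed**

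- Capsules alone: 840 − n < 0.80 × 840 = 672, so n > 168. That is more than 168/420 = 40% of intakes, or 168/3 = 56 days' worth.
- Pooled: 1,680 − n < 0.80 × 1,680 = 1,344, so n > 336. That is more than 336/420 = 80% of intakes, or 336/3 = 112 days' worth.

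The first row breaches the limit on either count and the second on neither. In the third, the outcome depends on how compliance is counted.

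**What the drug counts would show**

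By week 2, 84 capsules are due, and a one-capsule patient would have 42 of them left. Between weeks 8 and 20, 504 are due, and 252 would be left. With no visit in those 12 weeks, that surplus is first counted at the end of treatment.

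**The case against.** The strongest reply is that the label permits the protocol dose, since its range includes two. The synopsis and section 5.4.1 are unambiguous, so no site reading the protocol would prescribe one capsule. The label also says nothing about the tablets, so patients must learn the double-dummy regimen from another source, and that source would presumably state two of each. Section 12.2 adds that "All investigators at each study site should attend a training session before participation".

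The protocol also has a check on intake. Section 5.3 states "Subjects should be advised to return all unused drugs at each study visit" and has staff record the number of capsules, and section 12.3 asks for close follow-up of poor compliers. A patient with half the capsules left at week 2 would be hard to miss, and correction then leaves compliance at 95% or better. A switch to one capsule only after week 8 is unlikely, because the label has not changed since the first day. Any bias would run against XXK and could not produce a false claim of superiority.

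Most of this stands, and it limits the likely size. It does not remove the contradiction. Drug counts detect a low dose after the fact and leave the printed instruction as it was. Oral advice to take two would compete with a label that says one is acceptable. The late-switch pattern shows how long the unmonitored interval is; it is not a forecast. Dilution of the test arm also matters in a trial designed to show superiority.

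**Conclusion.** The label contradicts the regimen and should be corrected. For a patient taking one capsule at every intake the result does not depend on the counting rule: half the capsules due, 300 instead of 600 mg of XXK a day in the trial arm, and compliance of 50% or 75%, both below 80%. This rests on section 5.4.1 as the amount due; the pooled figure also needs full tablet intake.

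The effect on the trial's results cannot be quantified. The protocol gives no basis for estimating how many patients would take one capsule, so neither a PPS loss nor a power loss can be stated. The FAS retains such patients if they have evaluable follow-up. The expected direction is dilution of the XXK arm. Confidence is high about the wording conflict and its consequence for such a patient, and does not extend to any effect on the trial's conclusion.

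**What to change.** In section 5.2, (2) Labeling, replace the dosing line with two capsules per intake, three times a day, to match section 5.4.1 and the synopsis. For packs already printed and issued, send sites a notice that the dose is always two capsules and that patients should be told to disregard the lower figure.

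The cost is one label line and one notice, with no new data and no change to the analysis. For packs already blinded and packaged, the notice is the practical remedy. Packs not yet labelled, including any for the 160 patients added in section 3.3, can carry the corrected line. A patient who follows it takes 840 of 840 capsules, 600 mg of XXK a day in the trial arm, with 100% capsule compliance.
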